
#### Comparison condition: usual care wait-list control (UC)

Participants who are allocated to the UC condition receive the ACTIVATE intervention for approximately 12 weeks following their last chemotherapy infusion. They are advised to continue with their regular activities of daily living during chemotherapy. No exercise restrictions are made.

### Data collection

#### Primary outcome

##### Objective assessment of cognitive functioning

At four of the five study timepoints (i.e., baseline (pre-intervention), end of chemotherapy (post-intervention/post-wait period; primary endpoint), 16-weeks post-chemotherapy (first follow-up), and at 1-year post-baseline (second follow-up)), participants complete a neuropsychological test battery that is used to compute a composite cognitive summary score (COGSUM). The battery covers verbal and visual memory, attention/working memory, and processing speed, and was chosen because these cognitive domains have been shown to be sensitive to adverse effects of chemotherapy in previous studies [54]. Moreover, the specific tests were chosen because they have accounted for most of the between-group variance observed with a larger test battery [54]. The order of tests is as follows: Hopkins Verbal Learning Test Revised (verbal memory [63]), Brief Visuospatial Memory Test Revised (visual memory [64]), Weschler Adult Intelligence Scale-IV (WAIS-IV) Digit-Symbol Coding (processing speed [65]), WAIS-IV Letter-Number-Sequencing (working memory [65]), Auditory Consonant Trigrams Test (working memory [66]), Controlled Oral Word Association Test (working memory [67]), and Trail Making Test A and B (processing speed and cognitive flexibility/task switching capacity [68]). To reduce practice effects, different testing forms are used at each timepoint, with the exception of the WAIS-IV tests, Controlled Oral Word Association Test, and Trail Making Tests A and B, where alternate forms are not available.

#### Secondary outcomes

##### Self-reported cognitive functioning

At each of the five study timepoints, participants complete self-report questionnaires assessing cognitive functioning and its impact on quality of life. These include the Functional Assessment of Cancer Therapy-Cognitive Function (FACT-Cog) Version 3 [69, 70] and the Patient-Reported Outcomes Measurement Information System Applied Cognition short form [71–73].

##### Brain functioning and structure (MRI/fMRI and EEG)

Optional neuroimaging (i.e., MRI/fMRI) and EEG are completed in a sub-set of interested and eligible participants at three timepoints: baseline (pre-intervention), end of chemotherapy (post-intervention/post-wait period; primary endpoint), and at 1-year post-baseline (second follow-up). The MRI assessment is a 60-min scan comprised of a high-resolution structural scan, a resting state fMRI procedure, a diffusion tensor imaging sequence, and two fMRI tasks designed to measure working memory (i.e., Letter N-Back Task [74] and recognition memory (i.e., Word List Recognition Task [75]). These tasks were selected as physiological differences (e.g., brain activity) have been observed from pre- to post-chemotherapy during these tasks in women treated for breast cancer [75, 76]. Imaging takes place with a Siemens Biograph 3 Tesla Magnetom MR Scanner equipped with a 12-channel head coil. All data will be analysed with SPM12 and FSL.

The EEG assessment (Vancouver site only) is performed using a 64-channel Hydrogel Geodesic SensorNets (EGI, Eugene, OR). Five minutes of resting data are collected while participants have their eyes closed. Participants then perform a 25-min modified visual sustained attention to response task (SART) while their EEG is recorded, where they are asked to respond to a serial sequence of digits and withhold responses to any letters that appear [77–80]. EEG results are recorded and amplified using the Net Amps 300 amplifier at a sampling rate of 250 Hz. Scalp electrode impedances are under 50 kΩ. The signals are referenced to the vertex (Cz) and filtered from 4 to 40 Hz. A notch filter at 60 Hz is applied. The EEG signals will be analyzed offline using Brain Electrical Source Analysis (BESA; MEGIS Software GmbH). An automated artifact scan available by BESA is performed for extracting motion and excessive eye movement artifacts.

#### Other outcomes

##### Socio-demographic and medical information

Age, civil status, level of education, and annual household income are collected using a self-report questionnaire at baseline (pre-intervention). Medical information on disease stage, treatment protocol, and current medication use are obtained from medical records at baseline (pre-intervention) and at 1-year post-baseline.

##### Psychological health and quality of life

The Hospital Anxiety and Depression Scale [81], Perceived Stress Scale [82], the RAND 36-Item Health Survey 1.0 [83], FACT-Breast Version 4 [84], and FACT-Fatigue [71] are used to assess anxiety and depressive symptoms, perceived stress, health-related quality of life, breast cancer-related quality of life, and cancer-related fatigue, respectively. These are completed by participants at each of the five timepoints.

##### Physical fitness

Aerobic capacity (VO_2_ peak) is measured with a maximal CPET using a metabolic cart (PARVO Medics in Vancouver and VMAX CPET System in Ottawa) performed by trained technicians/respiratory therapists and staff in medically supervised settings. Resting heart rate, measured using electrodes, and resting blood pressure (mmHg), measured in duplicate on the non-surgical side using a blood pressure monitor, are done as precursory steps to ensure participants are able to perform the physical assessments [50]. Anthropometrics include participants’ height (measured with a stadiometer) and weight (measured on a standard scale) while they wear light clothes and no shoes. These outcomes are assessed at baseline (pre-intervention), end of chemotherapy (post-intervention/post-wait period; primary endpoint), 16-weeks post-chemotherapy (first follow-up) for the UC group (optional), and at 1-year post-baseline (second follow-up).

##### Physical activity

Self-reported physical activity behaviour is assessed using a modified version of the Godin Leisure Time Exercise Questionnaire [85]. This is measured at all five study timepoints.

##### Adherence and attendance to the ACTIVATE intervention

Adherence to the supervised exercise prescription and attendance to supervised exercise sessions are tracked by exercise trainers weekly for enrolled participants. Attendance is defined as number of sessions attended compared to number of prescribed sessions. Adherence is defined as number of sessions where the exercise target was achieved for duration and intensity (i.e., percent of HRR). Reasons for missed exercise sessions or non-adherence to the prescribed exercise targets (duration or intensity) are collected by exercise trainers. Participants track their adherence to the home-based exercise prescription throughout the intervention using a logbook. To improve adherence to the ACTIVATE intervention, participants’ parking expenses are covered and exercise sessions are scheduled around their medical appointments, observed holidays, and personal schedules. Also, exercise sessions are offered on weekdays and weekends during regular working hours, as well as early mornings and evenings.

##### Plan to promote participant retention

To help promote participant retention in the trial, participants are provided with a “report card” upon completing the 1-year follow-up assessment. This report card outlines their performance on the neuropsychological test battery (presented in percentiles), body composition, and CPET scores at each timepoint.

### Statistical analyses

Descriptive statistics will be computed for baseline socio-demographic and medical characteristics. Baseline socio-demographic and medical characteristics will be compared between participants who have completed assessments and those who dropped out in order to assess for attrition bias. Characteristics commonly associated with attrition (e.g., age, length of chemotherapy) will be included as covariates in all analyses under the assumption of “missing at random”. Analyses will be on an intent-to-treat basis, with per-protocol analyses considered as exploratory.

The primary outcome (i.e., cognitive functioning as indexed by COGSUM scores) will be analyzed using repeated measures ANOVA with fixed terms for time and a treatment by time interaction (constrained baseline differences). The stratification factors (i.e., study site and menopausal status) as well as factors associated with attrition (e.g., age and length of chemotherapy) will be included as covariates in the analyses. Correlation in repeated measures on the same individual over time will be accounted for by explicitly modeling the covariance matrix, with the best-fitting covariance structure decided using likelihood ratio tests and information criteria. The difference between the EX and UC groups at end of chemotherapy (primary comparison) will be calculated as adjusted least square mean difference in change from baseline, together with 95% confidence intervals. 

To test the effect of timing of the aerobic exercise (i.e., during versus post-chemotherapy) on outcomes at 1-year post-baseline, the models as described above will additionally include the response at 1-year follow-up and the contrast of interest will be the difference in change from baseline to 1-year after the start of chemotherapy. The sustainability of the intervention will be examined in each group by testing the change in response from immediately post-chemotherapy (post-intervention/post-wait period) to 1-year post-baseline, together with a 95% confidence interval.

Changes in secondary outcomes will be analyzed based on repeated measures ANOVAs with fixed terms for time and a treatment by time interaction, and adjusting for the same covariates identified for the primary outcome analysis (e.g., study site, menopausal status, age, length of chemotherapy). Correlation in repeated measures on the same individual over time will be accounted for by explicitly modeling the covariance matrix, with the best-fitting covariance structure decided using likelihood ratio tests and information criteria [86]. The difference between the EX and UC groups post-chemotherapy (primary endpoint) will be calculated as adjusted least square mean difference in change from baseline, together with 95% confidence intervals. All tests will be evaluated at the two-sided 5% level of significance. SAS [87] will be used for all analyses.

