#### Sample size

A power calculation was performed to detect changes in cognitive functioning (as measured by a composite cognitive summary score (COGSUM; developed by Collins et al. [52–55]). Using a minimum clinically important difference of 0.4 standard deviation units between EX versus UC at post-chemotherapy (i.e., post-intervention/post-wait period; primary endpoint), a total sample size of 74 women is needed to achieve 80% power using an analysis of covariance (ANCOVA) at a two-sided 5% level of significance. The correlation with the baseline measure was assumed to be 0.8. To account for a potential dropout rate of 10%, a sample of 84 participants (42 per condition) will be recruited.

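### Choosing the covariance structure by best fit on the trial data can move the true type I error of the nominal 5% tests modestly away from 5%; an unstructured matrix fixed in advance avoids this at almost no cost.

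*Protocol article*

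**What the plan says.** All references are to the protocol article.

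- **Model.** Under Statistical analyses, COGSUM is analysed by a repeated measures ANOVA with terms for time and treatment by time, and with the baseline difference constrained. Stratification factors and factors linked to attrition are covariates.
- **Covariance rule.** The within-person covariance is modelled explicitly, "with the best-fitting covariance structure decided using likelihood ratio tests and information criteria". The paragraph on secondary outcomes repeats the rule.
- **Primary contrast.** "The difference between the EX and UC groups at end of chemotherapy (primary comparison) will be calculated as adjusted least square mean difference". The scale is change from baseline, and a 95% confidence interval goes with it.
- **Level.** "All tests will be evaluated at the two-sided 5% level of significance".
- **Visits.** The section on objective assessment says that the battery is given "At four of the five study timepoints": baseline, end of chemotherapy, 16 weeks post-chemotherapy and 1 year. For the timing question, "the models as described above will additionally include the response at 1-year follow-up". The 1-year visit is therefore not in the primary model, which has two or three visits. The timing model can have four.

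**The concern.** In a constrained-baseline model, the standard error of the primary contrast depends on two quantities: the variance at end of chemotherapy and its correlation with baseline. Compound symmetry and other simple structures replace these with values shared across visits. COGSUM visits are unequally spaced, and chemotherapy falls between the first two, so equal variances and correlations are doubtful at exactly the visit that matters. With 74 to 84 women, fit criteria (BIC above all) can favour a simple structure that is wrong. The model-based standard error then treats that structure as known.

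At stake is whether the confidence interval and p-value of the primary comparison, and of the 1-year timing contrast, have their stated 95% coverage and 5% level. The error can go in either direction.

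**Working it through.** **1. The plan's own figure.** Inputs from Sample size: difference 0.4 SD, baseline correlation 0.8, 80% power, two-sided 5%.

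- Normal approximation per arm: 2 × (1.960 + 0.842)² × (1 − 0.8²) / 0.4² = 2 × 7.849 × 0.36 / 0.16 = 35.3, so 36 per arm, or 72.
- With the t distribution, 72 women give 79.6% power and 74 give 80.7%. The stated 74 is right.
- Dropout: 74 / 0.9 = 82.2, so 83, or 84 as an even total. This also agrees.

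The sample size is not affected by this point.

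**2. How pooling changes the size.** Label baseline 1 and end of chemotherapy 2. With complete data, the estimate is the difference in means at visit 2 minus b times the difference at visit 1.

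- Under a fitted structure with variance v and covariance c at both visits, b = c/v and the model-based variance is proportional to v − c²/v.
- The true variance is proportional to s₂² − 2b·s₁₂ + b²·s₁².
- With r² = true/model, the approximate size is 2 × P(Z > 1.96/r).

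*Illustration A (assumed truth: three visits, all correlations 0.8, SDs 1, 1.15, 1; compound symmetry held fixed).*
- v = (1 + 1.3225 + 1)/3 = 1.1075; c = (0.92 + 0.80 + 0.92)/3 = 0.88; b = 0.7946.
- Model variance = 1.1075 − 0.7744/1.1075 = 0.408.
- True variance = 1.3225 − 2 × 0.7946 × 0.92 + 0.6314 = 0.492.
- r = √(0.492/0.408) = 1.098; 1.96/1.098 = 1.786; size about 7.4%.

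*Illustration B (assumed truth: SDs equal; correlation 0.8 for visits 1–2 and 0.7 for the other two pairs).*
- v = 1; c = b = 0.7333; model variance 0.462; true variance 1 − 2 × 0.7333 × 0.8 + 0.5378 = 0.364.
- r = 0.888; 1.96/0.888 = 2.207; size about 2.7%, which is conservative.

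These are sizes for a wrong structure held fixed. Selection often moves to a better structure, so size after selection lies closer to 5%.

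**3. Size after selection, by simulation under no effect.** 2,500 trials per scenario (Monte Carlo SE √(0.05 × 0.95/2500) = 0.44 points), 84 women, 10% lost before the primary visit, constrained-baseline REML, four covariates. Candidates: CS, AR(1), Toeplitz, CSH, ARH(1), unstructured (CS and unstructured only with two visits). Assumed truths: baseline to end-of-chemotherapy correlation 0.8 (0.7 in one pattern), SD at end of chemotherapy equal, +15% or +30%, four correlation patterns.

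| Visits | AIC | LRT | BIC | Unstructured, fixed |
|---|---|---|---|---|
| 2 | 5.4–5.7% | 5.4–5.8% | 5.4–5.8% | 5.4–5.5% |
| 3 | 4.6–5.6% | 4.8–5.8% | 4.7–6.5% | 4.5–4.9% |
| 4 (timing model) | 4.7–7.1% | 4.5–7.3% | 4.6–8.7% | 5.2–5.5% |

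With no selection, a wrong structure held fixed gave 2.8–9.2% with three visits and 1.9–12.2% with four.

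**4. A second check.** 3,600 null trials per scenario (Monte Carlo SE 0.36 points), 76 women.
- Three visits, including truths where the baseline to end-of-chemotherapy correlation is the lowest and the variance rises: BIC about 5.5–8.2%, LRT 5.3–6.7%, AIC 5.1–6.3%, fixed unstructured 4.8–5.7% on the same data.
- Two visits: about 5.8% after selection against 5.3% unstructured.

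**5. What selection saves.** An unstructured matrix for k visits has k(k + 1)/2 parameters: 3, 6, 10 and 15 for 2, 3, 4 and 5 visits. For COGSUM the saving is small.

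**The case against.** The case for leaving the rule alone has real substance.

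- **The primary model is small.** A reader might infer from the four COGSUM assessments that the primary test itself runs at 7–10%. Four-visit simulations can produce such figures: with the baseline to end-of-chemotherapy correlation set to 0.70 and the others at 0.76–0.82, AIC or BIC selection gave 7.0–9.6%. The article does not support that reading, because it adds the 1-year response only for the timing analysis. Those runs also depart from the article's assumed correlation of 0.8. This objection stands, and with two visits there is almost nothing to correct.
- **The criterion matters.** The highest figures come from BIC. The article names likelihood ratio tests first, and these stay under 7% with three visits. This stands as a limit on size.
- **No steering.** A reader might infer that the rule lets the analyst choose a favourable result. The Blinding section keeps the statistician unaware of allocation, and the rule selects on fit. Taking the smallest p-value over candidates would give 5.6–10.0% with three visits, but the rule does not allow it. Blinding does not, however, repair a standard error from a misspecified structure.
- **SAP content.** A candidate list, degrees-of-freedom method or robust variance may be set out in a plan that is not shown, and their absence is no finding. The point rests on the data-driven rule that the article does state. A candidate list would narrow that rule without removing it.
- **Common practice.** Selection by fit is conventional, and a flexible rule may help in the optional imaging and EEG subset. The first does not protect the 5% level. The second is a reason for a fallback there.

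**Conclusion.** The concern holds in a limited form. The stated rule can move the size of the nominal 5% tests, usually upward and sometimes downward.

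For the primary comparison the drift is negligible with two visits. With three it is at most about 1.5 points in the main simulations and about 3 points in the least favourable BIC case of the second check. The four-visit timing contrast is more exposed, up to about 8.7% in the main simulations.

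Several scenarios stay near 5%. All figures depend on assumed correlations, variances and candidate structures, and the article fixes only the 0.8 baseline correlation. The change is worth making because it costs little and makes the primary interval follow from one model stated in advance. It is not evidence that the primary test is seriously invalid.

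**What to change.** In Statistical analyses, replace the best-fit rule for the COGSUM models (two to four visits) with an unstructured covariance fixed in advance and Kenward-Roger degrees of freedom. Name one fallback, for example heterogeneous Toeplitz, to be used only if the unstructured fit does not converge. State also which visits enter the primary model.

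In the paragraph on secondary outcomes, apply the same rule to the five-visit questionnaire models (15 covariance parameters). For the optional MRI/fMRI and EEG subset, keep the same default with the prespecified fallback, since an unstructured fit may not converge in a small group.

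The cost is a sentence or two of text, a model option in SAS, a few degrees of freedom and a possible need for the fallback. The sample size stays at 74, recruited as 84.

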**Discussion:**

Aerobic exercise is a promising intervention for preventing and/or managing CRCC and enhancing quality of life among women diagnosed with breast cancer. The ACTIVATE trial tests several novel hypotheses, including that aerobic exercise can prevent and/or mitigate CRCC and that this effect is mediated by the timing of intervention delivery (i.e., during versus post-chemotherapy). Findings may support prescribing exercise during (or post-) chemotherapy for breast cancer and elucidate the potential role of aerobic exercise as a management strategy for CRCC in women with early-stage breast cancer.

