A parallel two-arm RCT will be undertaken to determine if aerobic exercise is an effective strategy to prevent and/or mitigate CRCC and its impact on quality of life among women who receive chemotherapy for breast cancer. The primary objective of the Aerobic exercise and CogniTIVe functioning in women with breAsT cancEr (ACTIVATE) trial is to test the effect of an aerobic exercise intervention initiated during chemotherapy (EX) compared to a usual care wait-list control group (exercise initiated post-chemotherapy; UC) on objectively measured cognitive functioning in women who receive chemotherapy for breast cancer. Secondary objectives are to: (1) test the effects of EX compared to UC on (a) self-reported cognitive functioning, (b) global and regional measures of brain structure and functioning with magnetic resonance imaging (MRI) and functional MRI (fMRI) focussing on areas underlying attention and working memory, and (c) overall global and regional brain network organization and neural functioning in areas underlying attention and working memory using electroencephalography (EEG), and; (2) assess if the timing of the intervention (i.e., during versus post-chemotherapy) moderates the effects of exercise. It is hypothesized that: (1) the EX group will perform better on neuropsychological tests (primary outcome) than the UC group post-chemotherapy (primary endpoint) and at other timepoints; (2) the EX group will maintain pre-chemotherapy brain structure and functioning post-chemotherapy and at other timepoints whereas the UC group will have significant changes in both, and; (3) the EX group will self-report better cognitive functioning and psychosocial outcomes (i.e., quality of life, psychological health, cancer-related fatigue) post-chemotherapy and at other timepoints compared to the UC group.

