#### The ACTIVATE intervention (EX condition)

The ACTIVATE intervention is delivered concurrently with participants’ chemotherapy regimen (starting up to 1 week before participants’ chemotherapy start date and lasting approximately 12–24 weeks for those in the EX group). Tables 1 and 2 provide an overview of the progressive aerobic exercise prescription. The intervention is based on prior protocols used by the study team for women receiving treatment for breast cancer or who have completed treatment for breast cancer [56–59]. Participants complete three supervised aerobic exercise sessions each week at the Breast Cancer Training Center or at the Chan Gunn Pavilion on the University of British Columbia campus for the Vancouver site, or at the University of Ottawa Behavioural and Metabolic Research Unit for the Ottawa site. Supervision of the exercise sessions is provided by trained exercise professionals who have a valid CPR-C certification and experience supervising exercise in chronic disease populations.

**Table 1 Tab1:** Details of supervised and home-based exercise prescription for participants on a 3-week chemotherapy cycle protocol

Cycle	Week	Supervised Program			Home-based Program		
		Freq.	Duration (minutes)	Intensity (% HRR)	Freq.	Duration (minutes)	Intensity (RPE)
1	1	3	20–25	50–55^a^, 55–60	0	0	0
	2	3	30	55–60	0	0	0
	3	3	25–30	60–65	1	15–20	12–13
2	4	3	30–35	50–55^a^, 60–65	1	15–20	12–13
	5	3	25–35	60–65, VT	1	15–20	12–13
	6	3	25–35	60–65, VT	1	20–30	12–13
3	7	3	35–40	55–60^a^, 60–65	1	20–30	12–13
	8	3	25–35	65–70, VT	1	20–30	12–13
	9	3	25–35	65–70, VT	1	20–30	12–13
4	10	3	35–40	55–60^a^, 65–70	1	20–30	12–13
	11	3	20–35	65–70, HIIT	1	20–30	12–13
	12	3	20–40	65–70, HIIT	1	20–30	12–13
5	13	3	40	55–60^a^, 65–70	1	20–30	12–13
	14	3	20–35	70–75, VT/HIIT^b^	1	20–30	12–13
	15	3	20–35	70–75, VT/HIIT^b^	1	20–30	12–13
6	16	3	40	55–60^a^, 65–70	1	20–30	12–13
	17	3	20–35	70–75, VT/HIIT^b^	1	20–30	12–13
	18	3	20–35	70–75, VT/HIIT^b^	1	20–30	12–13
7	19	3	40	55–60^a^, 65–70	1	20–30	12–13
	20	3	20–35	70–75, VT/HIIT^b^	1	20–30	12–13
	21	3	20–35	70–75, VT/HIIT^b^	1	20–30	12–13
8	22	3	40	55–60^a^, 65–70	1	20–30	12–13
	23	3	20–35	70–75, VT/HIIT^b^	1	20–30	12–13
	24	3	20–35	70–75, VT/HIIT^b^	1	20–30	12–13

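### The 1-year EX–UC contrast compares two exercise strategies: it cannot attribute a difference to timing alone, and the moderation and mediation wording is not supported

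*Protocol article*

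**What the plan says.** In the protocol article, secondary objective 2 (Background) is to "assess if the timing of the intervention (i.e., during versus post-chemotherapy) moderates the effects of exercise". The main Discussion repeats this aim. The Discussion paragraph of the Abstract puts the same hypothesis as "this effect is mediated by the timing of intervention delivery".

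The analysis that serves this objective is in Statistical analyses, where its purpose is given as "To test the effect of timing of the aerobic exercise (i.e., during versus post-chemotherapy) on outcomes at 1-year post-baseline". The repeated-measures model is extended to the 1-year response, and "the contrast of interest will be the difference in change from baseline to 1-year after the start of chemotherapy". Site, menopausal status and factors linked to attrition, with age and length of chemotherapy as examples, enter as covariates. The main Discussion adds that the design will allow outcomes to be related to timing, and so inform how exercise is best delivered.

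The two arms are described as follows:
- **EX:** the programme runs alongside chemotherapy, "lasting approximately 12–24 weeks for those in the EX group". On frequency: "Participants complete three supervised aerobic exercise sessions each week".
- **UC:** participants "receive the ACTIVATE intervention for approximately 12 weeks following their last chemotherapy infusion". For their activity during chemotherapy, "No exercise restrictions are made".

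**The concern.** Reading the 1-year difference as an effect of timing requires that the arms differ only in when the programme is given. They also differ in how long it is prescribed, because EX length follows the chemotherapy regimen while UC length is about 12 weeks whatever the regimen. A pure effect of programme length would then look like an effect of timing.

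The moderation wording raises a second question. It presupposes an exercise effect during chemotherapy and another after it, and asks whether they differ. By 1 year both arms have been offered the programme, so the trial has no reference group against which the post-chemotherapy effect can be estimated. What secondary objective 2 can conclude, and the advice on when to offer exercise that is meant to follow from it, depend on these two points.

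**Working it through.** **1. The plan's own figure.** The sample size concerns the end-of-chemotherapy comparison. With a difference of 0.4 SD and a baseline correlation of 0.8, the residual SD is √(1 − 0.8²) = 0.6. At two-sided 5% and 80% power, the normal approximation gives 36 per arm (72 in total). A t-based ANCOVA gives power 0.796 at 36 per arm and 0.807 at 37, hence 74. Dropout of 10% gives 37/0.9 = 41.1, rounded up to 42 per arm, hence 84. The stated figures reproduce, and nothing below changes them.

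**2. Prescribed programme.** Let L be chemotherapy length in weeks, 12 to 24 by the range given for EX. EX is prescribed L weeks and UC about 12. Sessions are 3 × weeks, assuming that UC also has three a week. Time since programme end at week 52 is 52 − L for EX and 52 − (L + 12) for UC. This counts week 52 from about the start of chemotherapy and assumes that UC starts right after the last infusion.

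| L | EX sessions | UC sessions | Ratio | Weeks since end, EX | Weeks since end, UC |
|---|---|---|---|---|---|
| 12 | 36 | 36 | 1.0 | 40 | 28 |
| 16 | 48 | 36 | 1.33 | 36 | 24 |
| 18 | 54 | 36 | 1.5 | 34 | 22 |
| 24 | 72 | 36 | 2.0 | 28 | 16 |

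Prescribed length matches only at about 12 weeks of chemotherapy. The recency gap is (52 − L) − (52 − L − 12) = 12 weeks at every L.

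**3. Why the length covariate does not help.** Suppose there is no timing effect and no fading, and that benefit is b per programme week. EX gains bL and UC gains 12b, so the arm difference is b(L − 12). A main effect of L shifts both arms equally at a given L. The arm term therefore still carries roughly b × (mean L − 12). Only an arm × length term could represent a difference that grows with L.

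**4. Illustration of size (assumed, not estimated).** Take 0.4 SD at 24 weeks, so b = 0.4/24. The apparent timing difference is 0 at L = 12, 0.4 × 4/24 = 0.07 SD at 16, 0.4 × 6/24 = 0.10 SD at 18, and 0.4 × 12/24 = 0.20 SD at 24. The article does not give the mix of regimens. Fading after the programme would push the other way by an unknown amount, so the net direction is not established.

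**5. Moderation and mediation.** Write m_EX and m_UC for the 1-year means and m_0 for the mean had nobody received the programme. The contrast m_EX − m_UC equals (m_EX − m_0) − (m_UC − m_0). No arm estimates m_0, so neither bracket is known. A contrast of zero fits two equal benefits and also no benefit at all. UC's own change from end of chemotherapy to 1 year cannot fill the gap. It is uncontrolled, and several of the tests have no alternate forms (Data collection, Primary outcome), so practice and natural recovery are mixed in. Mediation does not fit either: timing is what is randomized, not a variable on the path from treatment to outcome.

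**The case against.** The strongest reply is that the article defines timing as during versus after chemotherapy, and that these are exactly the two randomized strategies. The intent-to-treat contrast between them is unbiased for their difference and useful in practice. That stands. A reader might infer that the contrast can say nothing about timing; that goes too far. What it cannot do is separate timing from programme length.

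It can also be argued that m_0 cancels in step 5, so that the contrast is itself the difference between the two effects. Algebraically that is so, but it is a difference between packages of unequal length, and it does not show whether either package works at 1 year. This is less than the moderation wording promises.

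Four further readings are tempting and not supported:
- *That neither arm is without a programme after chemotherapy.* The article describes no post-chemotherapy programme for EX. What is missing is an arm that never receives it.
- *That the recency gap is a separate flaw.* At a visit fixed at 1 year, a later programme necessarily ends nearer the visit. The same applies to the tie between sessions and infusions, and the UC prescription is not detailed. These are limits to state.
- *That the weeks in the table are weeks since exercise stopped.* They are weeks since the programme ended. Exercise outside it may continue and is captured only by questionnaire.
- *That 0.2 SD is the expected bias.* It takes the longest regimen, a linear dose-response and no fading.

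**Conclusion.** The point holds in a limited form. The 1-year contrast is a sound randomized comparison of two strategies, but it is mislabelled as an effect of timing. Whenever chemotherapy exceeds about 12 weeks, prescribed programme length differs between arms, up to twofold at 24 weeks, and the planned covariate does not remove that. Recency differs by about 12 weeks as a consequence of delay. The effect of exercise after chemotherapy against none is not identified, so the moderation and mediation statements are not supported and a null result would be ambiguous.

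The session counts assume three supervised sessions a week in UC. The recency figures assume an immediate UC start and 12 weeks exactly. The start of up to one week early in EX, or any gap before UC begins, shifts them by that amount. The matter is secondary and falls short of a must-fix, since the primary comparison and the sample size stand.

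**What to change.** 1. In Statistical analyses and in both statements of secondary objective 2, describe the 1-year contrast as a comparison of two strategies: the programme during chemotherapy for its length, against about 12 weeks of it afterwards. Drop the moderation wording there and the mediation wording in the Abstract.
2. State the differences in prescribed length and in time since programme end as limits on interpretation. Qualify the Discussion's claim about guiding delivery accordingly, and say that a null contrast would not show that both strategies work.
3. Report weeks since programme end by arm at the 1-year visit.
4. Optionally, and as exploratory only, add an arm × planned chemotherapy length term. Planned length can come from the treatment protocol recorded at baseline. Report the contrast at about 12 weeks, where prescribed lengths match. Say with it that the estimate is imprecise (it sits at the edge of the length range with 74–84 women), that length is not randomized, and that recency is still unmatched (40 weeks in EX against 28 in UC).

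The cost is wording, one descriptive line and at most one model term. The fix does not touch the design, the sample size or the primary analysis.
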